### Assessments

All participants attend three visits (baseline and two follow-up) consisting of clinical neuropsychological, physical, and functional observations (baseline, 6 months, and 12 months). The study schedule is shown in Fig. 2. In these visits, participants undergo the following assessments: 1) clinical and sociodemographic assessment; 2) physical activity assessment; 3) accelerometry assessment; 4) neuropsychological assessment; 5) and brain imaging (MRI scan; this only at baseline). Informants (appointed by participants as the best available person to provide information about them) are also interviewed.

**Fig. 2 Fig2:**
[figure not shown]
Study schedule

In all assessments (baseline and follow-up clinical visits), the cognitive status of patients is classified into the following groups: 1) diagnosis of dementia; and 2) diagnosis of cognitive impairment with no dementia according to clinical, neuropsychological, and functional criteria. For this purpose, we used the usual criteria and definitions of the Diagnostic and Statistical Manual of Mental Disorders (edition 4 revised; DSM-4TR) [25]. At baseline, patients could only fulfil VCI without dementia defined as evidence of cognitive impairment and clinical consensus to identify significantly related vascular features; exclusion of dementia when impairments were not sufficiently severe to interfere with social or occupational functioning or when impairments were more focal than the global requirement for a diagnosis of dementia. For follow-up we considered the following criteria for subtypes of dementia: probable Alzheimer disease [26]; probable vascular dementia [27]; subtype of subcortical vascular dementia [28]; frontotemporal dementia [29]; and Lewy body dementia [30]. The criteria for Alzheimer’s disease with a vascular component was made when the investigator judged that the clinical picture presented both aspects of Alzheimer’s disease and vascular dementia.

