### Study outcomes

The primary outcome measure will be cognitive decline defined as a dichotomous variable (decline/no decline) through cognitive status criteria as described in the Assessments section below. The secondary outcomes are changes in neurocognitive scores of at least 1.5 standard deviation (SD) from baseline to endpoint (using *z* scores), a decline in the raw values of neuropsychological tests, in quality of life, functional and motor status, and falls.

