### Statistics

#### Sample size

The sample size calculation is based on two sets of data. In the LADIS observational prospective study, which included a similar population [13], there was progression in cognitive decline in 31% of the initial sample after 1 year of follow-up (200 participants out of 639 participants included). In the Osaki-Tajiri Project [72], which studied conversion to dementia in a similar population and measured different severities of cerebrovascular pathology (as in our study), odds ratios (ORs) between 2.12 and 6 were found to be implicated in the conversion into vascular dementia. We used an OR of 4 in our calculation of the expected effect (which is clinically significant).

Using Open Epi software [73] for sample calculation in randomised trials, we realised a number of 117 subjects in each arm with 95% confidence intervals (alfa of 0.05) and 80% power, giving a total of 234 subjects to be recruited. Loss to follow-up is usually 20% in this type of follow-up study, and thus a total of 280 subjects is estimated as being needed.

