#### Data analysis

Data will be registered according to the Consolidated Standards of Reporting Trials (CONSORT) guidelines for randomised controlled trials [19]. We will use intention-to-treat analyses as the primary analysis with all participants included according to initial group allocation. For the primary outcome analysis (dependent variable: cognitive decline according to clinical criteria), we will conduct a logistic regression analysis. Since the outcomes are measured at 6 and 12 months, we will fit a generalised estimating equations (GEE) logistic regression model for the data. The models will adjust for covariates which are assumed to interfere with cognition in the follow-up (age, gender, education, and baseline MoCA). For secondary outcomes, logistic or linear regression analysis will be used as applicable.

For each of the outcome endpoints (i.e. transition of cognitive status and change in neuropsychological evaluation through composite or global scores) the change from baseline to 6 months and 12 months will be assessed, even though we will consider 12 months as the primary marker of success.

Observing a statistically significant difference on any of the outcomes will be considered preliminary evidence of efficacy. We will also report variances, co-variances, and effect sizes, as well as sampling feasibility (i.e. ease of recruitment, recruitment rate, withdrawal rate).

The same qualified statistician involved in the statistical analysis designed the SAP and will independently review the analysis according to the plan.

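### The primary outcome as classified can only register conversion to dementia, but the sample size rests on a 31% rate of a differently described event, so 80% power is not shown for the endpoint analysed

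*Protocol article*

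**What the plan says.** Study outcomes defines the primary outcome as "cognitive decline defined as a dichotomous variable (decline/no decline) through cognitive status criteria as described in the Assessments section below". The criteria are in the Assessments section, in the text after the study schedule figure. There, for baseline and both follow-up visits, "the cognitive status of patients is classified into the following groups: 1) diagnosis of dementia; and 2) diagnosis of cognitive impairment with no dementia". The same paragraph fixes the starting state: "At baseline, patients could only fulfil VCI without dementia". The further criteria it lists for follow-up are all for dementia subtypes. Data analysis describes the endpoint in the same spirit, as one part of "transition of cognitive status and change in neuropsychological evaluation through composite or global scores", and names 12 months as the main time point.

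The Sample size section uses two sources. From an observational cohort (200 of 639 participants): "there was progression in cognitive decline in 31% of the initial sample after 1 year of follow-up". From a second study, of conversion to dementia: "odds ratios (ORs) between 2.12 and 6 were found to be implicated in the conversion into vascular dementia". It then states "We used an OR of 4 in our calculation of the expected effect", and reports that "we realised a number of 117 subjects in each arm with 95% confidence intervals (alfa of 0.05) and 80% power". That makes 234 in total, raised to 280 for a 20% loss.

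**The concern.** With two classes and every participant starting in the better one, there is only one possible worsening: from no dementia to dementia. The protocol places score changes of at least 1.5 SD and falls in raw test values among the secondary outcomes, so they are not a lesser step within the primary.

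The rate offered for planning carries a different description, progression in cognitive decline, while the odds ratio comes from conversion to dementia. The calculation thus joins a rate and an effect measure that the text attaches to differently described events. The rate needed for the endpoint, dementia at 12 months in the control arm, appears nowhere.

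What is at stake is how a null result would be read. If dementia is much less frequent than 31%, 117 per arm may give well under 80% power, and readers relying on the stated power would take such a result as stronger evidence of no effect than it is.

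**Working it through.** **Inputs.** Control rate 31% (200/639 = 0.313), odds ratio 4, alpha 0.05 (taken as two-sided, since 95% confidence intervals are named), power 80%, 117 per arm: all from Sample size. Allocation 1:1: Randomisation and masking. The control dementia rate is not given; 5 to 20% is my assumption.

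**Method.** Single 12-month comparison of two proportions, pooled variance under the null:

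- p1 = odds/(1 + odds), where odds = [p0/(1 − p0)]/OR
- n per arm = [1.960·√(2p̄(1 − p̄)) + 0.842·√(p0(1 − p0) + p1(1 − p1))]² / (p0 − p1)², with p̄ the mean of p0 and p1
- power = Φ{[(p0 − p1)·√n − 1.960·√(2p̄(1 − p̄))] / √(p0(1 − p0) + p1(1 − p1))}

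**Step 1: the plan's own figure.** p0 = 0.31 has odds 0.449; divided by 4, p1 = 0.101. Then p̄ = 0.2055 and n = (1.120 + 0.465)²/0.209² = 57.5, that is 58 per arm, or 67 with continuity correction. The stated figure is 117. Power at 117 per arm: (0.209·√117 − 1.120)/0.552 = (2.261 − 1.120)/0.552 = 2.07, so 98%, not 80%.

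Variations do not recover 117 from these two inputs: one-sided gives 46 (55 corrected), 90% power gives 77 (86), an odds ratio of 4 upwards (64.3%) gives 35 (41), and 31% taken as the average of both arms gives 42 (49).

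Other inputs do return about 117:

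- 31% against 15.5%: 116
- 31% against 48.8% (odds ratio 2.12): 118
- 15% against 4.2% (odds ratio 4): 117
- 5% against 17.4% (odds ratio 4, continuity correction): 117

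The text therefore does not show which rate produced the 80%.

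**Step 2: power for conversion to dementia at 117 per arm.** Example at 10% with odds ratio 4: p1 = 0.027 and (0.789 − 0.676)/0.341 = 0.33, so 63%.

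| Assumed control dementia rate | Power, OR 4 | n per arm for 80%, OR 4 | Power, OR 2.12 |
|---|---|---|---|
| 5% | 37% | 349 | 18% |
| 10% | 63% | 175 | 31% |
| 15% | 80% | 117 | 42% |
| 20% | 90% | 88 | 52% |

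An odds ratio of 2.12 is the low end of the range the protocol cites. With an odds ratio of 4, power reaches 80% at a control rate of 14.9%.

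**The case against.** Several points on the other side stand.

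- The shortfall is conditional. At the protocol's own odds ratio, 117 per arm is enough if at least about 15% of controls convert within 12 months, and nothing in the document excludes that.
- A reader might infer that dementia will be rare and the trial therefore underpowered. The document gives no conversion rate. Its functional entry criterion is an alternative (unchanged daily activities or a MoCA not in the dementia range), so preserved function is not required of everyone. Rarity is plausible but not documented.
- A reader might infer that the 31% counts any worsening at all. The protocol does not say what the cohort counted as progression; it only describes that event differently from the endpoint.
- A reader might assume that 31% produced the 80% power through a halving of risk, because 31% against 15.5% fits. The protocol never states a halving, and 15% with an odds ratio of 4 fits equally well.
- A clinical-status endpoint is a legitimate choice, and decline short of dementia is still captured by the secondary outcomes.

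What these points do not answer is that the endpoint and the cited rate are described as different events, that no dementia rate is given, and that the stated sample size does not follow from the stated inputs. The planned GEE model over 6 and 12 months with covariates could move the power somewhat, but it does not supply the missing rate. Nor is this detail left to an analysis plan that is not shown: the article itself states both the classification and the calculation.

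**Conclusion.** The point holds as a mismatch between endpoint and planning rate, together with a sample size that does not reproduce. It does not hold as a demonstrated loss of power. The 80% is not shown for the endpoint analysed. With an odds ratio of 4, power at 117 per arm runs from 37% at a 5% control dementia rate to 90% at 20%, crossing 80% at about 15%; with an odds ratio of 2.12 it runs from 18 to 52%. These figures assume a two-sided test, a single 12-month comparison, 117 evaluable per arm and control rates that I have supplied. The plan needs correcting because, as written, a reader cannot tell what event the trial was sized to detect.

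**What to change.** Before unblinding, make the primary endpoint and the planning rate the same event, by one of two routes.

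1. If conversion to dementia is meant: state the assumed 12-month dementia rate in each arm with its source, recompute, restate the power for 117 per arm, and limit the conclusions to what that power supports.
2. If a broader decline was intended: define the step short of dementia in the Assessments section, from data already collected, and restate the power with a rate for that same event. The 1.5 SD rule listed under the secondary outcomes should not be assumed to correspond to the 31%; nothing in the protocol links the two.

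Under either route, give the two proportions, the sidedness and the formula, so that the number per arm can be reproduced.

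The cost is changed wording and a recalculation, with no new data. The restated power may be less favourable, and the second route makes the primary event less severe than dementia.

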### Assessment measures

Participants are interviewed regarding sociodemographic factors relevant to the study subject and clinical factors, including cognitive status in a neurological assessment and functional status evaluation with the modified Rankin scale and the National Institutes of Health Stroke Scale (NIHSS) [31–33].

### Neuropsychological and quality of life assessments

Cognitive evaluation follows the same protocol in all assessments and is applied by a trained neuropsychologist. It consists of a neuropsychological battery specifically designed for this study in order to be sensitive for vascular cognitive deficits and includes the following tests: The Montreal Cognitive Assessment (MoCA) [34, 35] for general assessment; Letter cancellation [36] and the Wechsler Adult Intelligence Scale-Revised (WAIS-R) Digit Span (forward) [37, 38] for the assessment of attention and concentration; Verbal Fluency [35], Trail-Making Test [39–41], Wechsler Adult Intelligence Scale-3rd edition (WAIS-III), Digit-Symbol [42], and Stroop Test [43, 44] to assess executive functions; the California Verbal Learning Test-9 (CVLT-9) [45, 46], Wechsler Memory Scale (WMS) Visual Reproduction and Logical Memory subtests [36, 47], and WAIS-R Digit Span (backward) subtest [36, 37] to assess memory; and the Alzheimer's Disease Assessment Scale (ADAS) Naming objects and Following Commands subtests [48, 49] to assess language. The impact of cognitive performance on daily living activities is assessed with the Instrumental Activities of Daily Living (IADL) [50]; the presence of depressive symptoms and apathy are assessed using the 15-item Geriatric Depression Scale [51] and the Apathy Evaluation Scale [52, 53], respectively.

The quality of life and other specific measures for the assessment of an individual psychological resources and the economic impact of the disease are also added in this protocol. These measures include the Euro Qol-5 [54] and the Quality of Life in Alzheimer’s Disease (QOL-AD) [55, 56], the 13-item Orientation to Life Questionnaire to measure Antonovsky’s sense of coherence (SOC-13), a health-promoting resource which strengthens resilience where higher scores indicate an ability to adapt to stressful situations [57–59], the Successful Aging Index (SAI) [60], an a priori index model of successful ageing which was validated with respect to service use, and the Resources used in Dementia Interview (RUD) [61] to collect data on resource utilisation to calculate costs of care (healthcare resource utilisation) and time dedicated to caregiving in dementia.

### Physical activity assessment

The Functional Physical Fitness Battery [62] is a simple, reproducible, readily available tool to assess submaximal functional capacity and to evaluate the response to intervention. The Six-Minute Walk Test (6MWT) is performed around an 18-m line to measure the distance in metres walked in 6 min. Participants are instructed to walk at their own pace according to their tolerance to exercise for 6 min, with rest stops as needed.

The 30-s chair stand assesses lower body strength, which is needed for numerous tasks such as climbing stairs or walking. Participants are instructed to sit and stand as fast as they can in 30 s with arms folded across the chest.

To assess lower body flexibility (which is important for good posture, normal gait patterns, and for various mobility tasks, such as getting in and out of a bathtub or car), the participant is asked to start from a sitting position at the front of the chair, with one leg extended and hands reaching toward the toes. The distance in centimetres between the extended fingers and the tip of the toe are measured in both legs. To assess upper body (shoulder) flexibility (which is important in tasks such as combing one’s hair, putting on overhead garments, and reaching for a seat belt), the participant is asked to reach over the shoulder with one hand and up the middle of the back with the other hand. The distance in centimetres between the extended middle fingers is measured.

The agility/dynamic balance is assessed by the number of seconds required to get up from a seated position, walk 2.44 m, turn, and return to the seated position. In this framework, it is interesting to measure multiple dimensions of balance in different sensory environments; therefore, the Fullerton Advanced Balance Scale (FAB) is also applied [63]. The FAB comprises 10 items that are scored using a 0–4 ordinal scale (only eight items are used due to safety and functional reasons). In this case, the highest score possible on the test is 32 points. Items include standing with the feet together and eyes closed, reaching forward to retrieve an object (a pencil) held at shoulder height with an outstretched arm, turn 360 degrees in both right and left directions, a tandem walk, standing on one leg, standing on foam with the eyes closed, a two-footed jump, and a walk with head turns.

### Accelerometry assessment

The physical activity (PA) time of each participant is assessed by accelerometry (ActiGraph, GT3X+ model). The accelerometer is a device that measures the acceleration of normal human movements, ignoring high-frequency vibrations associated with mechanical equipment. All participants are asked to wear the accelerometer on the right hip, close to the iliac crest, for a week. The device activation, download, and processing is performed using Actilife v.6.13.3 software (ActiGraph, Fort Walton Beach, FL, USA). The devices are activated on the first day before the interview and data are recorded using the raw mode with a 30-Hz frequency and posteriorly downloaded into 15-s epochs.

A valid day is defined as having 600 min (10 h) or more of monitor wear and all participants with at least 3 valid days (including 1 weekend day) are included in the analyses. Accelerometer counts ≥ 100 counts per minute (cpm) are classified as PA with additional separation into light intensity (100–2019 cpm) and moderate-to-vigorous intensity (≥ 2020 cpm) [64, 65]. There are no cut-offs for the sedentary time using the three-axial information from this new generation Actigraph GT3X+ accelerometer; therefore, we used the previous cut-offs which are based on the vertical axis only. Compliance with PA recommendations for public health is assessed according to the WHO recommendations (adults: 150 min/week of at least moderate-to-vigorous intensity defined as ≥ 21.4 min/day).

### Neuroimaging assessment

Besides confirming eligibility for the study, MRI is further used to control for confounders (for instance, information on the degree of atrophy, severity, number and localisation of vascular lesions, and presence of strategic lesions). MRI uses the following sequences: Fast Spin Echo, Fast Flair, T1 W-3EDGE (MPRAGE), diffusion and SWI, using a previously defined protocol based on the LADIS European study [66]. The parameters that are measured include:Atrophy (Scheltens evaluation, score 1–8 for global atrophy and 0–4 for temporal lobe atrophy) [67];White matter change evaluation using Modified Fazekas scale for severity (score 1–3) [68] and Scheltens scale for localisation of the lesions [67];Number and localisation of microbleeds (SWI sequences);Number and localisation of lacunes;Description of previous infarcts and intracerebral haemorrhages and silent infarcts.

MRI is conducted on the total sample at baseline. In all centres the MRI machine will have the same power (3 T).

To check for adhesion to the MRI protocol and the quality of scans, the performance of a dummy run will be required before the start of the study. For validation, the representative images of the dummy run will be checked centrally before start inclusion, and corrections will be made if necessary.

MRI will have a central reading, blinded to the clinical details, conducted by the responsible neuroradiologist. A clinical neurologist ([name]) not involved in the clinical assessment will also review the images blinded to the clinical results.

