### Randomisation and masking

After the 4-week run-in period, research personnel not involved in the recruitment, assessment, or intervention are responsible for managing the randomisation process using a statistical program. The randomisation sequence is generated by R software [69]. Participants are randomly assigned (1:1) to either the intervention group (IG) or to the best practice usual care group (CG), stratified by gender.

All follow-up assessments (physical, neuropsychological, and clinical diagnosis), and also the neuroradiological evaluation, are blinded to treatment allocation, as well as in the data set registry.

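### Baseline MRI is said to serve confounder control, but no stated model contains an MRI variable; the cost is some precision, not validity

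*Protocol article*

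**What the plan says.** The Neuroimaging assessment section gives the baseline scan two purposes: "Besides confirming eligibility for the study, MRI is further used to control for confounders". Its examples are the degree of atrophy, the severity, number and site of vascular lesions, and strategic lesions. The data should be nearly complete and of good quality: "MRI is conducted on the total sample at baseline", all machines have the same field strength, and the reading is central and blinded.

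The Data analysis section then states the adjustment: "The models will adjust for covariates which are assumed to interfere with cognition in the follow-up (age, gender, education, and baseline MoCA"). No MRI variable is on that list. For secondary outcomes it says only that logistic or linear regression will be used as suits the outcome.

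Under Randomisation and masking, allocation is 1:1 and "stratified by gender", with no other factor named.

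The Sample size section draws on an outside cohort that "measured different severities of cerebrovascular pathology (as in our study") and reports that "odds ratios (ORs) between 2.12 and 6 were found to be implicated in the conversion into vascular dementia".

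**The concern.** The Data analysis section chooses covariates by one criterion: they are assumed to affect cognition during follow-up. The Neuroimaging section calls lesion burden and atrophy confounders, which puts them under the same criterion. Yet they are not on the list, and the randomisation does not balance them by design. As the article stands, the scan is given an analytic role that no described model carries out.

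Two things are at stake. The first is precision on the primary outcome, obtainable from data already collected. The second is how the model is chosen. If the sponsor later acts on the stated purpose, it must pick among two atrophy scores, white matter severity and site, microbleeds, lacunes and infarcts, with nothing to say which. Protection of type I error holds for a model fixed in advance, not for one picked from several after the results are seen.

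**Working it through.** **Inputs from the article.** 117 per arm; alpha 0.05 (taken as two-sided, from the 95% confidence level); 31% decline at one year, used as the control risk; odds ratios 2.12 to 6 from the outside cohort; 4 as the odds ratio for the expected effect.

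**Assumptions.** One binary MRI marker with prevalence 25% or 50% (30% or 50% in the imbalance step), odds ratio 2.12, 4 or 6 for decline, and independent of the planned covariates. A single time point stands in for the GEE model.

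**The plan's own figure.** The article gives no figure on MRI adjustment, so 117 per arm is taken as given. It does not follow from 31% and an odds ratio of 1/4 (10.1% in the intervention arm): the usual two-proportion formula then gives 58 per arm. Halving the risk to 15.5% (odds ratio 0.41) gives 116. That is a separate matter, but it is why three treatment odds ratios are shown.

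**Precision.** Without the marker, z = |ln(marginal OR)| / √[1/(117·p0(1−p0)) + 1/(117·p1(1−p1))]. With the marker, z = |ln(treatment OR)| / SE, where SE comes from the expected information of a logistic model with intercept, arm and marker. Power = Φ(z − 1.96). Relative efficiency is the squared ratio of the two z values.

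Example: treatment OR 0.40, marker OR 6, prevalence 25%.
- Without the marker the OR appears as 0.452, so z = 0.795/0.318 = 2.50 and power is 0.706.
- With it, z = 0.916/0.344 = 2.66 and power is 0.759.
- Relative efficiency is 1.133.

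Results at 25% prevalence:

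| Treatment OR | Marker OR | Power without | Power with | Relative efficiency |
|---|---|---|---|---|
| 0.25 | 2.12 | 0.963 | 0.965 | 1.017 |
| 0.25 | 4 | 0.951 | 0.961 | 1.061 |
| 0.25 | 6 | 0.936 | 0.956 | 1.108 |
| 0.40 | 2.12 | 0.789 | 0.797 | 1.020 |
| 0.40 | 4 | 0.749 | 0.779 | 1.075 |
| 0.40 | 6 | 0.706 | 0.759 | 1.133 |
| 0.50 | 2.12 | 0.588 | 0.597 | 1.021 |
| 0.50 | 4 | 0.542 | 0.575 | 1.081 |
| 0.50 | 6 | 0.498 | 0.552 | 1.145 |

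At 50% prevalence the gains are of the same size. Overall the gain is about 0 to 5 points of power, worth about 2% more sample at marker OR 2.12, 6–8% at OR 4 and 10–15% at OR 6.

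**Validity.** With no treatment effect and the marker left out (50% prevalence, 200,000 simulated trials per case), type I error was 0.050, 0.051 and 0.050 for marker ORs 2.12, 4 and 6.

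**Chance imbalance.** The SD of the between-arm difference in marker prevalence q is √[2q(1−q)/117], which is 6.0 points at q = 30% and 6.5 at q = 50%. A difference of 10 points or more in either direction then has probability 9.5% or 12.6%.

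Its effect on the risk difference, with 31% vs 15.5% decline and the marker's effect averaged over the two arms:
- Smallest case (OR 2.12, q = 50%): risks are 23.1% vs 38.9% in controls and 10.7% vs 20.3% in the intervention arm. The shift is 0.10 × (15.8 + 9.6)/2 = 1.3 points.
- Largest case (OR 6, q = 30%): risks are 19.1% vs 58.7% and 7.8% vs 33.6%. The shift is 0.10 × (39.6 + 25.8)/2 = 3.3 points.

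Both compare with a risk difference of 15.5 points.

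**The case against.** The best defence is that the Neuroimaging section does not say the control takes place in the primary model. The Objectives include a search for determinants of cognitive progression, where lesion burden would be a natural covariate. The secondary models are open, and an SAP that is not shown may place MRI scores in any of these. This stands against a stronger reading that a reader might infer, namely that MRI adjustment never happens. The document shows only that no described model contains it. The defence does not remove the mismatch for the primary model, because the covariates there are listed, not deferred.

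A reader might also infer that the plan's own sources show MRI severity to be strongly prognostic here. They do not. The odds ratios concern conversion to vascular dementia in an observational cohort. The article does not say which exposures carry them, whether they were adjusted for age or baseline cognition, or how they relate to this trial's scales. Age, education and MoCA are already in the model, so any correlation with lesion burden would shrink the gains above.

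A third inference is that the treatment estimate is confounded. In a 1:1 randomised comparison it is not. Chance imbalance is already reflected in the confidence interval, and adjusting for four covariates is a defensible choice.

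Finally, a reader might take "White matter change evaluation using Modified Fazekas scale for severity (score 1–3") to mean that a clear scan must be graded as mild disease. The article does not say so. The modified scale is cited but not shown, and the list of measured parameters is not presented as complete.

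**Conclusion.** The point holds as an inconsistency within the article: MRI is assigned confounder control, while the stated primary model and the stratification contain no MRI variable. The two sections need to be brought into line. The consequence is limited to about 0 to 5 points of power and a chance of roughly one in ten to one in eight of an uncorrected imbalance of 10 points or more, which would move the risk difference by 1.3 to 3.3 points. There is no bias and no inflation of type I error for a model fixed in advance. The power range is upper-end. It assumes that a binary marker at the chosen prevalence carries the cited odds ratios independently of MoCA, age and education. This is a worthwhile, cheap correction and not a threat to the trial's validity.

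**What to change.** In the Data analysis section, add one or two named baseline MRI scores from the blinded central reading to the covariates of the primary cognitive model, for example white matter severity and temporal lobe atrophy. Fix the choice, and how each score is coded, before unblinding, so that no marker is picked after the results are known. State how participants without a usable scan are handled. The cost is one line of text, one or two extra model parameters and the missing-scan rule; no new data are needed.

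If the sponsor prefers to keep the four covariates, the alternative is to reword the Neuroimaging assessment section so that it gives MRI only the purposes the analysis will serve, such as eligibility, description of the sample and the determinants analysis.
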